### **2.3 Trial statistics**

#### **Statistical methods**

#### **Sample size for original study**

Worthing Audit data Feb 2010-July 2010: 3400 patients admitted through the Acute Medical Unit:

n= 1746 with a pre-admission creatinine (51.3%)

Of this cohort n=184 had AKI on admission (11%) 1561 (88%) did not

Of remaining group n=1219 did not develop AKI

N=95 (7%) developed AKI during admission

Figure 1: Patient Flow Chart

[figure not shown]

Figure 1 – flow chart for initial derivation of Acute kidney injury physiological scoring (APS) system. Based on 6 months data and a cohort of 1746 patients who had a recent creatinine result.

|                              | Incidence | Hospital mortality |
|------------------------------|-----------|--------------------|
| AKI on admission to hospital | 11%       | 19%                |
| Hospital acquired AKI        | 7%        | 20%                |

The initial retrospective validation on the St Richard's site will involve a similar number of patients to enable statistical significance in terms of incidence of acute kidney injury to be assessed. A similar number of patients will then be assessed prospectively once the Acute kidney injury alert is introduced onto the Worthing site to allow comparisons between the two sites.

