## **1.2 RATIONALE FOR CURRENT STUDY**

As the 2009 NCEPOD report highlighted, AKI is a common medical complication that is often diagnosed late and in many cases predictable and avoidable. From our own Worthing Hospital Audit data over six months through the Acute Medical Unit, AKI on admission to hospital had a prevalence of 11%. In addition, 7% of patients subsequently developed AKI during admission. Overall mortality for this combined group of patients with AKI was 19-20%.

Our innovative scoring system - the **Acute Kidney injury Prediction Score (APS)** - utilising physiological measurements, biochemical parameters and known co-morbidities can identify patients at risk of developing AKI following hospital admission. This can then deliver near real-time alerts to nursing and medical staff and will advise on a care bundle.

We would like to retrospectively externally validate the scoring system at another site to add methodological rigor. We will use two parallel interrupted time-series studies, on the Worthing & Chichester sites at WSHT, with segmented linear regression analysis in order to evaluate the longitudinal effect of intervention (use of the score and subsequent alert) and controls for trends in outcome.

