### 3. STUDY DESIGN

2 parallel interrupted time-series design studies, on the Worthing & Chichester sites at WSHT, with segmented linear regression analysis in order to evaluate the longitudinal effect of intervention & controls for trends in outcome.

Initially (Phase 1) we will retrospectively review both sites to validate the score. Using the Chichester site this will add external validity to the APS score.

The alert will then be instituted (Phase 2) at the Worthing site during which time both sites will be monitored for the incidence of Acute kidney injury and adherence to the Patienttrack Assessment Pack at the Worthing site. After interim analysis, the plan will then be to roll-out the alert to the Chichester site and further analyses will then be performed.

Worthing and Chichester are relatively close geographically and demographics are similar making the use of the Chichester site as the initial 'control' arm methodologically sound. If there are significant differences in the two populations in terms of AKI incidence and outcomes, they will be picked up in the initial Phase 1 part of the study

Duration: 24 months

Cohort: All medical patients admitted as emergencies to WSHT two sites Acute Medical Units (AMU) and Becket ward and spend at least one night as an in-patient.

**Baseline data collection:** data will be retrieved from the Patienttrack, Pathology & PAS databases relevant to the 'AKI Patienttrack Assessment Pack'. This data will be transferred to an excel spreadsheet and then anonymised. This data will be stored on the WSHT server & only hospital password protected computers will be able to access this data. Anonymised data for mathematical & statistical analysis will be transferred by password protected & encrypted memory sticks or secure NHS e-mail.

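### Cohorts sized by a six-month patient count, with no calendar windows and no allowance for season, leave within-site estimates, above all the Chichester step, open to a seasonal artefact

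*Protocol*

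**What the plan says.** Section 2.3 of the protocol takes its size from an earlier audit: "Worthing Audit data Feb 2010-July 2010: 3400 patients admitted through the Acute Medical Unit". The analysable part is "n= 1746 with a pre-admission creatinine (51.3" per cent of those, and the caption to Figure 1 confirms the span: "Based on 6 months data and a cohort of 1746 patients who had a recent creatinine result".

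Two cohorts are then sized by reference to that count. For the Chichester validation, "The initial retrospective validation on the St Richard's site will involve a similar number of patients". For the alert period, "A similar number of patients will then be assessed prospectively once the Acute kidney injury alert is introduced onto the Worthing site". The protocol states no number of months, calendar months or number of time points for either.

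Section 3 gives a total of 24 months without dividing it. Chichester is observed alongside Worthing while the alert runs at Worthing only, and is called the initial control arm. The second step is open-ended: "After interim analysis, the plan will then be to roll-out the alert to the Chichester site and further analyses will then be performed". Sections 5 and 8.7 have the study team performing interim analysis at least monthly, so the date of that step is not fixed either.

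The analysis is segmented linear regression at two parallel sites, used "in order to evaluate the longitudinal effect of intervention (use of the score and subsequent alert) and controls for trends in outcome" (section 1.2, repeated in substance in sections 2.2 and 3). The protocol does not mention season.

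**The concern.** A patient count borrowed from February to July covers part of a year. If the series before and after a switch-on each cover only part of a year, a straight line fitted to the first part can read the seasonal curve as a trend and project it forward. The departure from that projection is then credited to the alert. The sign and size of the error depend on the go-live month, which the protocol leaves open.

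Emergency medical admissions could plausibly vary by season in ways that affect AKI, although the protocol gives no figure. At stake is whether a within-site level or slope change can be read as an effect of the alert. The exposure is greatest at the Chichester step, because both sites then have the alert.

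**Working it through.** **The plan's own figures.** 1746/3400 = 51.35%, as stated. February to July inclusive is 6 months. For hospital-acquired AKI, "N=95 (7%) developed AKI during admission" against 1219 without it gives 95/(1219 + 95) = 95/1314 = 7.2%, consistent with the stated 7%. The protocol gives no effect size, power or number of time points, so there is no sample-size calculation to reproduce.

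**Months implied by a similar number.** The audit rate is 3400/6 = 567 admissions a month, or 1746/6 = 291 a month with a prior creatinine. Like for like, a similar number takes 6 months. On mixed readings it runs from 1746/567 = 3.1 months to 3400/291 = 11.7 months. All are under a year. This uses Worthing's rate, as Chichester's is not given.

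**Model.** Take a noise-free monthly AKI rate with no alert effect,

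y(t) = 7% × [1 + a·cos(2π·month/12)],

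and fit

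y = b0 + b1·t + b2·post + b3·post·(t − n_pre)

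by least squares for each of the 12 possible start months. The amplitude a = 0.10 (±0.7 percentage points, pp) is assumed. All errors scale with a, so a = 0.05 halves them. The 6+6 layout follows the audit span. The 8+8 layout is 24/3 months, which applies only if all three states (no alert, Worthing only, both sites) lie inside the 24 months.

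Largest single-site errors at a = 0.10, as a share of the 7% rate:

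| Months before + after | Level change b2 | Difference in plain means |
|---|---|---|
| 6+6 | 13.5% (0.95 pp) | 12.4% (0.87 pp) |
| 8+8 | 20.6% (1.44 pp) | 7.0% (0.49 pp) |
| 12+12 | 18.8% (1.32 pp) | 0 |
| 24+12 | 13.5% (0.94 pp) | 0 |

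Hand check of the 6+6 mean: the six highest consecutive cosine values sum to 0 + 0.5 + 0.866 + 1 + 0.866 + 0.5 = 3.732. The two half-years therefore differ by 2 × 3.732/6 = 1.244 amplitudes, and 1.244 × 0.7 pp = 0.87 pp.

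For scale, a 25% relative reduction from 7% is 1.75 pp.

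**What removes the error.** Whole years bring the plain mean difference to zero but leave the level error. One sine/cosine pair in the model brings the level error to zero in every layout, at a price in precision. The binomial standard error (SE) of one month's rate with 1314/6 = 219 patients is √(0.07 × 0.93/219) = 1.72 pp. Propagated through the fit, the SE of b2 is:

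| Months | No seasonal term | With sine/cosine pair |
|---|---|---|
| 6+6 | 2.0 pp | 4.2 pp |
| 12+12 | 1.4 pp | 2.1 pp |
| 24+12 | 1.2 pp | 1.4 pp |

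**Two-site contrast.** If both sites have the same seasonal pattern, the error in the Worthing-minus-Chichester level change is 0. If their amplitudes differ by 20%, the worst case at 6+6 is 0.20 × 0.95 = 0.19 pp.

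**The case against.** The strongest reply is that the design already has a control. Section 3 monitors Chichester while the alert runs only at Worthing, and section 2.3 says the cohorts are meant for comparison between sites. A reader might infer from the short windows that season and alert cannot be separated at all. The documents do not support that: season shared by both sites cancels in the two-site contrast at the first switch-on. A staggered two-site model with month effects stays identifiable at the second step too, even with six-month blocks, provided Worthing's effect is stable by then. What remains is that the protocol describes two parallel series, never says that the segmented effect is the between-site difference, and specifies no staggered model.

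Two other stronger readings also fail. Not every phase is sized by the audit: the pre-alert series and the post-roll-out period have no stated length. Nor must all three states fit inside 24 months, because Phase 1 is retrospective and its baseline may lie outside them.

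On size, the amplitude is assumed and the figures are worst cases over start month. At 6+6 the average level error is 8.5%, and the worst case of 0.95 pp is below one SE (1.8 to 2.0 pp at 291 to 219 patients a month). That is fair. Sampling noise dominates in short series, but it does not remove the bias. At 12+12 without a seasonal term the worst case (1.32 pp) is about the size of the SE (1.2 to 1.4 pp).

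Finally, seasonal terms are commonly left to a statistical analysis plan, which is not at hand. Window length is different, because it is fixed by design. With 6+6 months, adding the term later roughly doubles the SE to 4.2 pp, more than half of the 7% baseline.

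**Conclusion.** The concern holds for within-site estimates. The protocol ties the Chichester validation cohort and the post-alert Worthing cohort to a count from half a year, sets no calendar windows, and names control for trends only. At an assumed ±10% relative season, a single-site level change can be wrong by up to about 14% of the baseline rate with 6+6 months and 21% with 8+8, and a plain mean difference by up to about 12% with 6+6. At ±5% these halve.

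The first switch-on is protected to the extent that the sites share a season and the two-site contrast is the estimate used. The Chichester step is the most exposed, as no untreated site remains. The figures rest on the assumed cosine season and on the 6+6 and 8+8 layouts, which the protocol does not itself fix. They were computed for AKI incidence only and say nothing about the size of any error in mortality or length of stay.

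**What to change.** 1. Name the Worthing-minus-Chichester controlled contrast as the primary effect estimate for the first switch-on.
2. Define the windows by calendar time rather than patient count. Extract a longer pre-alert series at both sites, ideally 24 months, and compare whole years or the same calendar months before and after. Include respiratory rate and AVPU from Patienttrack where available: objective 2a concerns patients at risk, and section 3 feeds those two observations into the risk algorithm.
3. Add harmonic or calendar-month terms to the segmented regression. Longer windows alone do not remove the level error (still 18.8% at 12+12).

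The cost is a larger query on databases that the protocol already plans to use, plus a few model terms, with no added patient contact. The same-month option compares fewer months and so loses some precision.

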### 3. STUDY DESIGN

2 parallel interrupted time-series design studies, on the Worthing & Chichester sites at WSHT, with segmented linear regression analysis in order to evaluate the longitudinal effect of intervention & controls for trends in outcome.

Initially (Phase 1) we will retrospectively review both sites to validate the score. Using the Chichester site this will add external validity to the APS score.

The alert will then be instituted (Phase 2) at the Worthing site during which time both sites will be monitored for the incidence of Acute kidney injury and adherence to the Patienttrack Assessment Pack at the Worthing site. After interim analysis, the plan will then be to roll-out the alert to the Chichester site and further analyses will then be performed.

Worthing and Chichester are relatively close geographically and demographics are similar making the use of the Chichester site as the initial 'control' arm methodologically sound. If there are significant differences in the two populations in terms of AKI incidence and outcomes, they will be picked up in the initial Phase 1 part of the study

Duration: 24 months

Cohort: All medical patients admitted as emergencies to WSHT two sites Acute Medical Units (AMU) and Becket ward and spend at least one night as an in-patient.

**Baseline data collection:** data will be retrieved from the Patienttrack, Pathology & PAS databases relevant to the 'AKI Patienttrack Assessment Pack'. This data will be transferred to an excel spreadsheet and then anonymised. This data will be stored on the WSHT server & only hospital password protected computers will be able to access this data. Anonymised data for mathematical & statistical analysis will be transferred by password protected & encrypted memory sticks or secure NHS e-mail.

**Introduction of 'AKI Patienttrack Assessment Pack' to WSHT:** every night PAS will be searched for relevant AKI score diagnosis on every new admission within the last 24hrs & this will be fed into the 'AKI' algorithm. Biochemistry will similarly be searched for the worst eGFR in the last 6/12 to identify the diagnosis Chronic kidney disease (CKD) for the AKI score. RR & AVPU will be fed directly from Patienttrack into the algorithm. Therefore we will be able to identify those patients 'at risk of AKI' who have been admitted within the last 24 hours & this will be displayed using a traffic light system on the patient chart within the AKI Patienttrack Assessment Pack. In addition real time Creatinine results will be fed into the AKI Patienttrack Assessment Pack to highlight 'confirmed AKI' using the same traffic light system. This is demonstrated pictorially below:

## PAS – Semahelix

- Age
- Coded diagnosis
  - Liver Failure
  - CCF
  - DM

**Biochemistry Results** –  
Worst eGFR in last 6/12  
(=CKD diagnosis)

Pulled into patient  
chart overnight

## AKI ALGORITHM

RR  
AVPU

### Biochemistry Results – Real time Creatinine

[figure not shown]

(Abbreviations: AVPU level of consciousness – Alert/Vocal/Pain/Unresponsive; CCF – congestive cardiac failure; DM – Diabetes; RR – Respiratory rate)

Results will be displayed within the patient chart as a traffic light system (No AKI, At risk, Confirmed AKI). If the patient displays 'At risk' or 'Confirmed AKI' then clicking over the traffic light key will take the clinician to a new screen displaying the Creatinine results graphically & a checklist for AKI. An automated AKI alert will be also sent at 0100 each day to the responsible Doctor with a 'read receipt' to acknowledge that the e-mail information has been received. All patients 'at risk' or 'confirmed AKI' will also appear on the AKI Hospital Patient List which can be accessed by the medical staff, Outreach staff & Renal team. This is displayed pictorially on the following page:

Main Patienttrack frontpage

[figure not shown]

Patient Chart

[figure not shown][figure not shown]

CLICK  
INTO

### AKI Hospital Patient List

- Name
- Hospital No
- Age
- Gender
- Consultant
- Ward
- Bed number
- Most recent Creatinine
- AKI status
  - At risk
  - Confirmed

CLICK  
INTO

[figure not shown][figure not shown]

### CHECKLIST

1. REVIEW FLUID BALANCE – correct hypovolaemia if appropriate
2. REVIEW DRUG CHART – stop nephrotoxins
3. EVIDENCE FOR SEPSIS? – investigate & treat urgently
4. INVESTIGATIONS
  - a. Urine Dip: If 'active' seek advice
  - b. Daily U&E, Creatinine
  - c. Consider U/S renal tract
5. PPI if oral nutrition poor
6. Avoid contrast media unless essential (seek advice)

(Abbreviations: U&E – urea and electrolytes; U/S – ultrasound; PPI – proton pump inhibitor)

**Educational Package:** pre & post implementation questionnaires will be distributed to nursing & medical staff to identify any educational requirements. An educational package will be delivered to all nursing & medical staff prior to implementation consisting of e-learning, paper educational tools & small group ward-based teaching by the Outreach teams.

**Post - Introduction of 'AKI Patienttrack Assessment Pack' to WSHT, data collection:** data will be retrieved from the Patienttrack, Pathology & PAS databases relevant to the 'AKI Patienttrack Assessment Pack'. This data will be transferred to an excel spreadsheet and then anonymised. This data will be stored on the WSHT server & only hospital password protected computers will be able to access this data. Anonymised data for mathematical & statistical analysis will be transferred by password protected & encrypted memory sticks or secure NHS e-mail.

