### **Research Question/ Main Aims:**

Phase 1 – is the APS externally valid? We will assess this by retrospective external validation of the score on the Chichester site.

Phase 2 - can the use of an electronic prediction & identification alerting tool to deliver an individualised care bundle for hospital in-patients at risk of or with confirmed AKI reduce:

1. The incidence of AKI in those patients 'at risk'
2. The harm (mortality, morbidity, Length of stay (LOS)) associated with failure to recognise those patients with confirmed AKI

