## 4. PARTICIPANT ENTRY

### 4.1 PRE-REGISTRATION EVALUATIONS

No additional tests will be performed in the study compared to if the patient was not in the study.

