## **6. ASSESSMENT AND FOLLOW-UP**

This is an initial in-patient study with no long-term follow-up planned outside of normal protocols.

The study ends on the patients discharge.

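### The alert prompts more creatinine testing where it is live, so AKI ascertainment may change together with the intervention and distort both Phase 2 objectives

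*Protocol*

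**What the plan says.** - **Intervention.** Protocol Section 3 describes a traffic-light flag on the patient chart: "If the patient displays 'At risk' or 'Confirmed AKI' then clicking over the traffic light key will take the clinician to a new screen", which shows the creatinine trend and a checklist. Item 4b of the checklist is "Daily U&E, Creatinine". The ultrasound item after it is worded as something to consider; the creatinine item is not.
- **Outcome.** The same section says that "real time Creatinine results will be fed into the AKI Patienttrack Assessment Pack to highlight 'confirmed AKI" status. Outcome data come from the Patienttrack, Pathology and PAS databases. The protocol sets no common creatinine schedule for the pre-alert period or the control site.
- **Comparison.** The alert starts at one site while AKI is counted at both: "The alert will then be instituted (Phase 2) at the Worthing site during which time both sites will be monitored for the incidence of Acute" (the sentence goes on to name the condition in full). Similar demographics are given as the reason for "making the use of the Chichester site as the initial 'control' arm methodologically sound". The analysis is a segmented linear regression of two parallel time series.
- **Objectives.** Section 2.1 sets two Phase 2 objectives. Objective 2a is AKI incidence in at-risk patients. Objective 2b, as worded in Section 1.1, is "The harm (mortality, morbidity, Length of stay (LOS)) associated with failure to recognise those patients with confirmed AKI".
- **Testing.** Section 4.1 states: "No additional tests will be performed in the study compared to if the patient was not in the study".
- **Follow-up.** Section 6 states: "The study ends on the patients discharge".

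**The concern.** The intervention prompts more frequent use of the test that defines the outcome, in the patients in whom the outcome is counted, and at first at one site only. If testing rises, three things follow even when the alert has no effect on the kidneys.

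1. More AKI is found in at-risk patients, so objective 2a is biased against the alert.
2. Within a patient, a peak creatinine or lowest eGFR taken over more samples can only be as extreme or more extreme. The listed outcome of acute deterioration in creatinine and eGFR therefore moves up too.
3. The confirmed-AKI group gains cases that would not otherwise have been found. If they are milder, mortality and length of stay per confirmed case fall, so objective 2b is biased in favour of the alert.

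A segmented regression estimates a change in level or slope at go-live. A change in testing at go-live has the same signature. The control site removes trends shared by both sites, and this change is not shared. Later roll-out to Chichester would repeat the pattern and could be taken for replication.

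**Working it through.** **Plan's own figure.** Section 2.3 gives 95 patients who developed AKI during admission, 1219 who did not, and an incidence of 7%. 95 / (95 + 1219) = 95 / 1314 = 7.2%, so the stated 7% is reproduced with 1314 as the denominator. Hospital mortality with hospital-acquired AKI is 20%, or 0.20 × 95 = 19 deaths.

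**Model.** Let s0 be the proportion of AKI detected under usual testing, s1 the proportion under the alert, and R the true relative reduction. Then

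observed risk ratio = (1 − R) × s1 / s0,

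and the true reduction that is exactly hidden is 1 − s0 / s1. The documents give neither s0 nor s1. Assume s1 = 1.0 and take s0 = 0.9, 0.8 and 0.7.

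| s0 | Observed incidence, no true effect | RR, no true effect | RR, true 20% reduction | True reduction hidden |
|---|---|---|---|---|
| 0.9 | 7.2% → 8.0% | 1.11 | 0.89 | 10% |
| 0.8 | 7.2% → 9.0% | 1.25 | 1.00 | 20% |
| 0.7 | 7.2% → 10.3% | 1.43 | 1.14 | 30% |

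With equal ascertainment (s1 = s0), a true 20% reduction shows as 0.80. Partial uptake shrinks the effect: s0 = 0.8 and s1 = 0.9 give a risk ratio of 0.9 / 0.8 = 1.125 under no effect, and hide 1 − 0.8 / 0.9 = 11%.

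The 7.2% refers to all audit patients without AKI on admission. The protocol gives no incidence for flagged patients. The risk ratios depend only on s1 / s0, so they apply to the at-risk group whatever its baseline.

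**Scale against chance.** This uses a plain two-proportion comparison with 1314 per group and two-sided 0.05. Both are assumptions: the protocol promises only a similar number of patients and does not state sidedness. An alert with no effect would then show a significant increase with probability of about 12%, 40% or 80% for s0 = 0.9, 0.8 or 0.7. This is a yardstick and not the power of the segmented regression.

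**Mortality among confirmed cases.** Detected cases become 95 / s0, so the extra cases are 95 / s0 − 95. With mortality m in the extra cases (assumed), case mortality = (19 + extra × m) / (95 / s0).

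| s0 | Extra cases | m = 5% | m = 10% | m = 20% |
|---|---|---|---|---|
| 0.9 | 10.6 | 18.5% | 19.0% | 20% |
| 0.8 | 23.8 | 17.0% | 18.0% | 20% |
| 0.7 | 40.7 | 15.5% | 17.0% | 20% |

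The fall from 20% appears with no benefit to any patient. If the extra cases are as severe as the rest (m = 20%), it does not appear.

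**What is not affected.** Deaths, days in hospital, renal replacement and critical-care transfers counted in all admissions do not depend on how many patients are labelled as AKI.

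**The case against.** - **The checklist advises; it does not order.** A clinician must open it, Section 8.2 describes it as a recommended bundle, and compliance is itself an outcome. If flagged patients already have near-daily blood tests, little changes. This stands. A rise in testing is to be expected, but the protocol neither documents it nor allows its size to be derived.
- **Section 4.1 may not contradict the checklist.** The sentence sits under pre-registration evaluations, and Section 8.2 treats the bundle as best practice and not as a research intervention. It can mean that the research adds no tests while care may change. A reader might infer a flat contradiction; the text supports an ambiguity that needs reconciling.
- **Objective 2b need not be restricted to confirmed AKI.** Section 3.1 lists mortality, length of stay and the rest without restriction. This stands for those outcomes in the whole cohort, but both statements of the objective name confirmed AKI, and no other denominator is fixed for it.
- **The change may not be confined to go-live at Worthing.** Education goes to nursing and medical staff before implementation, so testing could shift earlier and possibly at both sites. That would blur the bias without removing it.
- **Sampling rules belong in a statistical analysis plan.** For the details, yes. The intervention, comparator, objectives and no-extra-tests statement, however, are fixed in the protocol.
- **A stronger numerical reading is tempting.** Section 2.3 has 1561 patients without AKI on admission but only 1314 classified afterwards. A reader might take the other 247 as never retested and infer that measured incidence would rise from 95 / 1561 = 6.1% to 7.2%. The documents do not support this. The flow chart that may explain the 247 is not available, nothing shows that they would be flagged, and the protocol's own 7% uses 1314. On that basis, giving the 247 the same rate leaves incidence at 7.2% before and after.

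**Conclusion.** The concern holds as a risk of differential ascertainment. Each link is in the protocol: AKI is read from creatinine, the checklist prompts daily creatinine in flagged patients, and the alert starts at one site. It bears on objective 2a, on observed creatinine and eGFR deterioration, and on any analysis of objective 2b confined to confirmed AKI. The direction is upward for the first two; for the third it favours the alert only if the extra cases are milder.

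The size cannot be determined. The risk ratios of 1.11 to 1.43 rest on the assumption that usual testing finds 90% to 70% of what daily testing would find and that daily testing is fully taken up; less uptake means less bias. It would be too strong to conclude that AKI incidence will rise, or that the design as a whole cannot show a benefit. Whole-cohort harm outcomes remain interpretable on this point. The changes below are cheap and worth making before the alert goes live.

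**What to change.** 1. Define at-risk status by the same APS extract, from admission data only, at both sites in all periods. Use that fixed group as the denominator for objective 2a.
2. Test objective 2b on mortality, length of stay, renal replacement and critical-care escalation in all at-risk admissions. Keep results in confirmed AKI only as secondary.
3. Report, by site and period, the proportion of at-risk patients retested and the creatinine tests per patient-day. Add a sensitivity analysis of AKI using a common in-hospital sampling window. State its limit: it removes surplus results but cannot recover patients who were never retested. Because observation ends at discharge, later results should not be relied on.
4. Reconcile checklist item 4b with Section 4.1, stating that the alert may change creatinine testing. This concerns how the outcome is ascertained and takes no position on what testing should be done.

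The cost is some extra programming on databases already being extracted. The common-window analysis discards some results and gives a slightly lower measured incidence.

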### **8.2 CONSENT**

We will be placing posters in all wards where patient data will be analysed describing the purpose of the study and the care bundles (alert packs) being trialled. The alert being

instituted initially at Worthing recommends a bundle of best practice and as such is not a research intervention that could be consented for.

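### As written, pre-launch teaching has no site limit and bundle posters go up in every analysed ward, so Chichester may be exposed while it is the control and the effect at Worthing go-live may not isolate the alert

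*Protocol*

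**What the plan says.** **Design.** Protocol section 3 plans two parallel interrupted time series. Worthing goes first: "The alert will then be instituted (Phase 2) at the Worthing site during which time both sites will be monitored". Similarity of the two hospitals is given as the reason for "making the use of the Chichester site as the initial 'control' arm methodologically sound". Chichester switches later: "After interim analysis, the plan will then be to roll-out the alert to the Chichester site".

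**Intervention.** Section 1.2 says that the segmented regression is to "evaluate the longitudinal effect of intervention (use of the score and subsequent alert) and controls for trends in outcome". Teaching and posters are not named as part of it.

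**Teaching.** The Educational Package paragraph of section 3 says "An educational package will be delivered to all nursing & medical staff prior to implementation consisting of e-learning", together with paper materials and small-group teaching on the wards by the Outreach teams. The paragraph headed "Introduction of 'AKI Patienttrack Assessment Pack' to WSHT" and the matching post-introduction paragraph both refer to the whole trust, which holds both hospitals.

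**Posters.** Section 8.2 says "We will be placing posters in all wards where patient data will be analysed describing the purpose of the study and the care bundles". It gives no start date and does not say how much of the bundle is described.

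The protocol has no site-by-site teaching schedule, no closing date for the baseline and no transition period.

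**The concern.** An interrupted time series with a parallel control needs two things. The control must stay unexposed until its own switch, and the date used as the interruption must be the date on which care starts to change. The teaching and poster arrangements put both at risk.

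The checklist in section 3 covers fluid balance, the drug chart, sepsis and daily bloods. Staff can act on these without an alert, so teaching could change care by itself. If it reaches Chichester early, the control series moves too. If it reaches Worthing before go-live, part of any change falls before the interruption date.

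Section 3 mentions adherence monitoring only for Worthing, so altered practice at Chichester might not be seen. A later analysis plan can move a change point. It cannot restore a control that has already been exposed.

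**Working it through.** The protocol states no power, effect size or expected leakage, so there is no design figure to reproduce. The check is mainly textual.

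**Step 1: is Chichester covered?**
- *Posters:* the rule is every ward whose data are analysed. Section 3 says "during which time both sites will be monitored for the incidence of Acute kidney injury", so the Chichester wards qualify while they are the control.
- *Teaching:* the recipients are all staff and the timing is before implementation. Nothing limits this to Worthing, and the surrounding headings refer to the whole trust. This route rests on the unrestricted wording, so it is less firm than the poster route.

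**Step 2: what would each comparison estimate?** Let T be the effect of teaching on the AKI rate and A the further effect of the alert, taken as additive. Let k, from 0 to 1, be the share of T that reaches Chichester in its control period.
- Baselines closed before any exposure: Worthing changes by T + A and Chichester by kT. The contrast is (T + A) − kT = A + (1 − k)T.
  - k = 0 gives T + A, the alert with its teaching.
  - k = 1 gives A, the alert added to teaching.
  - Any other k gives a mixture that matches neither.
- Taught weeks left in the Worthing pre-period: part of T lies before the interruption. It tilts the pre-alert trend, and the level change at go-live no longer captures T + A.
- Uncontrolled Worthing series with a clean baseline: the change is T + A, so teaching is credited to the alert.

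The protocol fixes neither k nor the end of the baseline, so it does not determine which of these is estimated.

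**Step 3: direction.** If T lowers true AKI, leakage shrinks the contrast relative to T + A. The checklist also asks for daily creatinine. If teaching increases testing, recorded AKI at Chichester could rise and widen the contrast.

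**Step 4: scale, as illustration only.** Inputs:
- Control rate p = 95/(95 + 1219) = 95/1314 = 7.23%, from section 2.3, which agrees with the stated 7%.
- n = 1314 per site, assumed from the plan to study a similar number of patients.
- Two-sided α = 0.05; section 7 gives 0.05 but no sidedness.
- Assumed total relative reduction r, and assumed share L of that total effect leaking to Chichester.

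Rates are p(1 − rL) at Chichester and p(1 − r) at Worthing, so the difference is d = p·r·(1 − L). Power ≈ Φ[(d − 1.96·SE₀)/SE₁], with SE₀ the pooled and SE₁ the unpooled standard error.

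For r = 30%:
- L = 0: d = 7.23% × 0.30 = 2.17 points
- L = 25%: d = 2.17 × 0.75 = 1.63 points
- L = 50%: d = 2.17 × 0.50 = 1.08 points

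| r | Power, L = 0 | L = 25% | L = 50% |
|---|---|---|---|
| 20% | 32% | 21% | 12% |
| 30% | 64% | 43% | 23% |
| 40% | 89% | 69% | 39% |

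This is a simple comparison of two proportions, not the planned segmented regression, and r and L are not in the protocol. It shows only that leakage would matter if it were substantial.

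**The case against.** **Teaching may be meant site by site.** Implementation is staggered, so teaching before implementation could mean before each site's own launch, and ward teaching by Outreach teams fits that. This stands as a possible reading, but it is not written. Even on that reading, Worthing teaching precedes the Worthing alert date.

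**The posters are notices.** They appear only under consent, in place of individual consent, and nothing says that they reproduce the checklist. Their effect on care may be small and their start date is unknown. This stands: the text supports some awareness of the bundle at Chichester, not delivery of it.

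**The baseline may be clean.** Phase 1 is retrospective. A baseline closed before teaching would leave the Worthing pre-period unaffected. This also stands, though no closing date is fixed. A reader might infer that teaching is absorbed into the Worthing pre-trend; the document does not establish that.

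**Transition coding belongs in an analysis plan.** This is largely fair, and the plan was not at hand. Who is taught and when, however, is fixed by the protocol and cannot be repaired in analysis.

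**Common teaching could be defended.** With full and equal exposure and additive effects, the contrast isolates the alert added to teaching. That would be a legitimate aim, but the protocol neither states it nor schedules teaching to secure it.

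**Conclusion.** The point holds as a defect in what the protocol fixes. Taken literally, its wording allows the control site to receive the teaching, and some awareness of the bundle, before or during its control period. It also places Worthing teaching ahead of the interruption date. The between-site contrast and the level change at go-live may therefore not isolate the alert.

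Three stronger readings are not supported:
- *That Chichester certainly receives part of the intervention.* The wording permits this but does not schedule it.
- *That the bias is certainly toward no effect.* That requires teaching to lower true AKI without raising recorded AKI through more testing.
- *That a particular loss of power follows.* Both the effect and the leaked share are assumed. Even with no leakage, the illustration gives only 32% power at r = 20% and 64% at r = 30%, so low power would not be due to leakage alone.

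The size cannot be derived from the protocol. The point merits action because the change is cheap before launch and exposure cannot be undone afterwards.

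**What to change.** 1. In the Educational Package paragraph of section 3, name the recipients as *all nursing and medical staff at the site about to go live*, and state that Chichester staff are taught only just before their own roll-out.
2. Close the Worthing baseline before teaching starts. Treat the weeks from first teaching to go-live as a transition period excluded from the level-change estimate. As a sensitivity analysis, set the change point at the start of teaching.
3. Say in section 1.2 that the effect estimated is then that of the alert together with its teaching.
4. Keep the study-information posters at Chichester, but leave out the checklist content during its control period, subject to ethics approval because the posters stand in for individual consent.
5. Record teaching and poster dates by site.

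**Cost.** A few weeks of data are dropped, Chichester staff are taught later, and a second poster version needs ethics agreement. Any residual exposure through shared awareness would remain, but the recorded dates would let it be examined.
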